### Measures and Outcomes

The primary objective is feasibility and acceptability. We will quantify feasibility (eligibility, invitation, consent, recruitment rate, retention, attendance and adherence, fidelity, and data completeness) and acceptability (postsession satisfaction, perceived usefulness, and comfort; recommendation item scored from 0‐10). A priori thresholds are as follows: retention of ≥80%, attendance of ≥80% per session, fidelity of ≥80%, data completeness of ≥85%, no serious adverse events, acceptability mean of ≥4.0/5, and net promoter score of ≥30.

As a secondary objective, this study assesses quantitative outcomes using validated psychometric tools and qualitative dimensions using reflexive thematic analysis. Mixed methods integration will offer a comprehensive understanding of EDUSEXONCO’s effects on sexual rehabilitation and psychosocial recovery.

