### Sociodemographic and Clinical Characteristics

At session 1 (before the intervention), participants will complete a brief self-administered questionnaire capturing age, educational level, employment status, relationship status, parity, menopausal status, time since diagnosis and completion of primary treatment, cancer type and stage (self-reported), prior and current treatments (including topical vaginal estrogen), relevant comorbidities and medications, pelvic floor therapy history, and sexual activity and partner status. Sensitive items are optional and include a “prefer not to answer” choice.

Participants will complete the sociodemographic questionnaire and baseline FSFI and EORTC QLQ-C30 at session 1 and repeat the FSFI and EORTC QLQ-C30 at session 3. Focus groups and semistructured interviews will be audio recorded and transcribed verbatim; participant observation field notes and anonymous diaries will be collected after each session. Optional one-to-one counseling is not recorded; clinicians may keep brief field notes. Trained staff will enter data into REDCap (Research Electronic Data Capture; Vanderbilt University).

Before each in-person session, participants receive a telephone call inviting them to attend the session. During the call, transportation needs are assessed; if necessary, transportation is arranged by the research team. Participants are informed that meals and refreshments are provided free of charge. If desired, participants may bring an accompanying adult family member who may attend the group sessions but will not participate in interviews or individual counseling to maintain privacy and confidentiality. To uphold participants’ autonomy and freedom, all individuals are explicitly informed that voluntary withdrawal is allowed at any time without penalty. This ensures full participant control over involvement and minimizes the risk of perceived coercion.

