### Sample Size

The quantitative pretest-posttest sample size was calculated based on mean differences and an adjusted SD of 0.69, informed by prior studies such as Starting the Conversation, a pilot trial using the FSFI to assess sexual function in survivors of gynecological cancer [11]. Assuming a moderate effect size (*d*=0.5), a 95% confidence level, and 80% power, the estimated sample size is 60 participants. Calculations were performed using G*Power (Heinrich Heine University Düsseldorf), a standard tool for sample size estimation in mean difference studies.

For the qualitative strand, sample adequacy is guided by the information power principle—considering study aim, sample specificity, quality of dialogue, and analytic strategy—rather than numeric saturation targets [24]. We purposefully seek heterogeneity in survivorship stage and symptom profiles to capture a range of experiences relevant to sexual health education.

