### Analysis Plan

#### Quantitative Analysis

Continuous variables will be summarized as means with SDs or medians with IQRs depending on the distribution, assessed using the Shapiro-Wilk test. Categorical variables will be presented as absolute and relative frequencies. Primary analyses will evaluate within-group changes (session 1 vs session 3) in FSFI and EORTC QLQ-C30 scores. For continuous outcomes, paired 2-tailed *t* tests will be used when normality assumptions are met; otherwise, Wilcoxon signed rank tests will be applied. A 2-sided significance level of α=.05 will be adopted. Effect sizes will be reported (Cohen *dz* for paired *t* tests; *r* for the Wilcoxon signed rank test), along with 95% CIs and graphical representations of response distributions. Missing data will be described; if they constitute >5% and are plausibly missing at random, an exploratory sensitivity analysis using multiple imputation will be performed.

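### The only named sensitivity analysis runs when missing session 3 scores look missing at random, so loss that depends on a woman's own change is described but never tested

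*Protocol article*

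**What the plan says.** The Quantitative Analysis section sets the comparison: "Primary analyses will evaluate within-group changes (session 1 vs session 3) in FSFI and EORTC QLQ-C30 scores". The test follows from the distribution: "paired 2-tailed *t* tests will be used when normality assumptions are met; otherwise, Wilcoxon signed rank tests will be applied". Missing data are to be described. Beyond that, one sensitivity analysis is named, under two joint conditions: "if they constitute >5% and are plausibly missing at random, an exploratory sensitivity analysis using multiple imputation will be performed". No branch is given for missingness that is not plausibly at random, or for 5% or less.

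Under Sociodemographic and Clinical Characteristics, women complete the questionnaires at session 1 and "repeat the FSFI and EORTC QLQ-C30 at session 3". There is no score in between. Measures and Outcomes sets feasibility thresholds that include "retention of ≥80%, attendance of ≥80% per session" and data completeness of at least 85%.

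The Intervention section foresees pelvic pain flares and marked emotional distress as adverse events. Pretrial Piloting and Feasibility Testing reports that full-day sessions were a potential barrier.

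**The concern.** A paired t test or signed rank test needs both scores. A woman who stops before session 3 therefore drops out of the estimate altogether. If stopping is related to how she was responding, the completer change is not the change in the women enrolled. The stated rule then leads to description and nothing more.

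The data offer little with which to defend missing at random. There is no intermediate FSFI or QLQ-C30 score, and the diaries kept after each session are anonymous, so they cannot be linked to a woman's scores.

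The 5% trigger also does little work at the enrolment reported. With 13 women enrolled as of July 2025 (Results), one missing posttest is 1/13 = 7.7%. At that size the judgement about missing at random alone decides whether any check is run.

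What is at stake is the change score that the study reports and carries into the design of the later comparative study.

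**Working it through.** **Inputs from the protocol.** Planned enrolment is 60 (Sample Size: "80% power, the estimated sample size is 60 participants"), the effect size is 0.5 ("Assuming a moderate effect size (*d*=0.5), a 95% confidence level"), and the test level is given by "A 2-sided significance level of α=.05 will be adopted". Retention of 80% allows 12 of 60 lost and 48 completing.

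**The plan's own figure.** A paired t test with dz = 0.5, two-sided 0.05 and 80% power needs 34 women, so 60 is not reproduced for this design. The present point does not depend on that. With 60 women power at dz = 0.5 is about 97%, and with 48 it is about 92%. The issue here is bias, not power.

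**Assumptions (not in the protocol).** Changes are in units of the completers' SD (set to 1). The mean change x of the women lost is assumed. For the p values, leavers are also given SD 1 around x.

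**Step 1: mean change in all enrolled.** With loss p and completer change c, m = (1 − p)c + px.
- c = 0.50, p = 0.20, x = 0: 0.80 × 0.50 = 0.40.
- c = 0.50, p = 0.20, x = −0.25: 0.40 − 0.20 × 0.25 = 0.35.

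These are mean changes, not dz, because mixing the two groups alters the SD. If every missing change is set to exactly zero, the variance is 0.80 + 0.20 × 0.80 × 0.50² = 0.84, and dz = 0.40/√0.84 = 0.44.

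**Step 2: effect on the test.** The pooled variance is v = [47 + 11 + 48(c − m)² + 12(x − m)²]/59 and t = m/√(v/60).
- Completers, c = 0.30: t = 0.30 × √48 = 2.08 on 47 df, p = 0.043.
- All enrolled, x = 0: m = 0.24, v = (58 + 0.173 + 0.691)/59 = 0.998, t = 0.24/0.129 = 1.86, p = 0.068.

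| Completer change | Leavers' mean change | All enrolled | p |
|---|---|---|---|
| 0.50 (p = 0.001) | 0 | 0.40 | 0.003 |
| | −0.5 | 0.30 | 0.034 |
| | −1.0 | 0.20 | 0.19 |
| 0.30 (p = 0.043) | 0 | 0.24 | 0.068 |
| | −0.5 | 0.14 | 0.30 |
| | −1.0 | 0.04 | 0.78 |

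Significance is lost at about x = −0.60 for a completer change of 0.50, and at about x = +0.08 for 0.30.

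**Step 3: a caution on zero-filling.** If the 12 missing changes are all exactly zero, the 11 drops out of v: v = (47 + 0.173 + 0.691)/59 = 0.811, t = 0.24/0.116 = 2.06, p = 0.043. The estimate falls to 0.24 but the p value stays where it was, because identical filled-in values shrink the SD. The zero-change bound therefore informs the estimate. Its p value should not be relied on.

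**The case against.** Standard multiple imputation assumes missing at random, so withholding it when that is implausible is defensible. A reader might infer that the condition is perverse in itself, but that does not hold: running the imputation anyway would not test the informative case. Details such as delta shifts and imputation variables are also often left to an analysis plan, and none is shown here. This stands as a defence of the condition. It does not cover the rule as a whole, which the article states itself and which names no analysis for the other case.

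A reader might also infer that intervention-related leaving makes missing at random implausible and that the completer result is biased upward. The documents do not show either. Leaving because of session length need not depend on the unseen session 3 score. Pain and distress are foreseen as adverse events, not as causes of dropout. Women with little need of the program could stop too, which might bias the other way. What stands is that loss may depend on a woman's own change.

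At a completer change of 0.50 the test result is robust: zero change in leavers still gives p = 0.003. That is correct. The fragile case is a smaller effect.

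Finally, Prespecified Study Aims makes score change secondary, and Strengths and Limitations disclaims effectiveness estimates. Retention is itself a feasibility outcome, so loss will be visible. This limits the weight. Visible loss still leaves the estimate untested, and the limitations listed do not include informative dropout.

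**Conclusion.** The point holds at moderate weight. Followed exactly, the rule leaves informative loss at session 3 described but untested.

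At the accepted 20% loss, a completer mean change of 0.50 SD would be 0.40 among all enrolled if leavers did not change, and 0.35 if they worsened by 0.25 SD. A change of 0.30 would be 0.24, and nominal significance would be lost if leavers vary around zero as completers vary around their own mean. These figures rest on assumed leaver outcomes, an SD of 1 and full enrolment of 60. They show how far the estimate could move. They are not an estimate of actual bias.

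The protocol does not support the stronger claims that bias is certain, that it must be upward, or that 0.40 and 0.35 are dz values.

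**What to change.** Remove the missing-at-random condition as a gate on sensitivity analysis. Whenever session 3 scores are missing, report beside the completer result:

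1. The mean change with missing change set to zero. This is a bound only if leavers did not worsen on average. Report it as an estimate rather than by rerunning the test: zero-filling shrinks the SD, and the usual signed rank test discards zero differences.
2. A delta-shifted scenario for women who withdrew, giving the tipping point at which the conclusion changes.
3. The reasons for leaving.

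Keep imputation under missing at random as one scenario where numbers allow, using the baseline score and few predictors. Leave sessions attended out of that model, since it largely encodes who has a session 3 score. With very few women, the zero-change and shifted scenarios are enough.

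Set this down before the session 3 scores are analysed. The cost is a little more analysis work and no new data collection. The reported change may look less favourable.

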#### Qualitative Analysis

Reflexive thematic analysis will be used following the framework by Braun and Clarke [25], prioritizing researcher reflexivity and active theme development over codebook reliability metrics. The analytic process will include (1) familiarization with transcripts and field notes, (2) inductive semantic and latent coding, (3) initial theme generation, (4) theme review against extracts and the full dataset, (5) theme definition and naming, and (6) construction of an analytic narrative linking themes to research questions and quantitative findings. Two researchers will independently code an initial subset to capture diverse interpretations, followed by reflexive dialogue. Subsequent coding will be led by the primary analyst with iterative peer debriefs focused on interpretive rigor rather than forced consensus. Reflexivity memos and an audit trail (decision logs and code or theme evolution) will be maintained. Credibility will be supported through data triangulation and thick description, dependability and confirmability will be supported through the audit trail, and transferability will be supported through detailed contextual reporting.

#### Reflexivity and Trustworthiness

The qualitative team (clinicians and educators experienced in sexual health and oncology) will maintain a reflexive stance through positionality statements, analytic memos, and documented decision trails. Credibility will be obtained via prolonged engagement across sessions, reflexive peer debriefs, and participant “member reflections” focused on emergent interpretations (not transcript verification). Dependability will be ensured based on an audit trail (versioned codebooks, memos, and decision logs) and clear documentation of analytic moves. Confirmability will be derived from reflexive journaling and an evidentiary chain linking raw data to themes and interpretations. Transferability will be dependent on “thick” descriptions of the setting, participants, and delivery to support readers’ judgments of applicability to similar contexts.

#### Mixed Methods Integration

Integration will occur at the interpretation stage through meta-inferences and joint displays juxtaposing quantitative pretest-posttest changes (FSFI and EORTC QLQ-C30 scores) with qualitative themes (eg, sexual well-being, communication, agency, and body image). We will seek convergence, complementarity, and expansion; discrepancies will be explicitly examined to refine interpretations and inform practical recommendations.

### Pilot Test

EDUSEXONCO was developed through a structured, user-centered process with three phases: (1) formative co-design, (2) content finalization and manualization, and (3) pretrial piloting and feasibility testing.

### Formative Co-Design

We held participatory workshops with survivors (breast and gynecological cancer), clinicians (gynecological oncology, internal medicine, and psychiatry), and allied professionals (psychology, social work, pelvic floor physiotherapy, nutrition, yoga and relaxation, and sexual education). Workshops identified priority needs, culturally appropriate language, and acceptable delivery formats. Preliminary materials (slides, handouts, and 3D educational models) were iteratively refined using survivor feedback and brief “think-aloud” walk-throughs to optimize clarity, tone, and inclusiveness.

### Patient and Public Involvement

Survivors of breast and gynecological cancers contributed to co-design (prioritizing topics, refining language, shaping levels, and informing 3D educational models) and will continue to provide iterative feedback on content and delivery during the study. They will also be invited to participate in dissemination and the codevelopment of implementation recommendations for scale-up.

#### Content Finalization and Manualization

A multidisciplinary panel reviewed all modules against international guidance (WHO; United Nations Educational, Scientific, and Cultural Organization; and WAS) and local practice to ensure accuracy, cultural relevance, and inclusivity. We developed a facilitator manual (learning objectives, session flow, time allocations, materials, and scripts for sensitive topics); fidelity tools (checklists and attendance and adherence trackers); and brief staff training on stigma-free, rights-based communication. Minor wording and sequencing changes enhanced accessibility for diverse literacy levels.

#### Pretrial Piloting and Feasibility Testing

Core components were piloted with a convenience sample of eligible survivors (n=15) to assess feasibility (recruitment and retention, session length, and logistics), acceptability (satisfaction, perceived usefulness, and comfort discussing sexual health), and fidelity (adherence to the manual). During pretrial piloting, full-day sessions were identified as a potential feasibility barrier; consequently, contingency adaptations (shorter session blocks, optional hybrid delivery, and flexible scheduling) were prepared while preserving the protocol’s objectives and core content. In this study, brief participant and facilitator feedback will be reviewed after each session to inform minor, prespecified logistical refinements (eg, scheduling and session length and pace) for subsequent groups without modifying core content or learning objectives. These findings guided the final structure of the sessions and the implementation plan to be used.

### Ethical Considerations

The protocol was approved by the Research Ethics Committee of FVL (protocol 2024.248). All participants will provide written informed consent before enrollment. The informed consent form will outline study activities and the use of data for analyses aligned with the study objectives. Participation is voluntary, and patients may decline without any impact on the provision of usual clinical care. Participants will not receive financial compensation or additional services; however, the cost of transportation from their residence to FVL and a meal voucher will be covered.

Only trained team members will deliver content within their scope of practice. Any clinical, psychological, or emotional issues arising from the implementation of the EDUSEXONCO intervention are escalated to the study clinician and the psycho-oncology team, who are professionally qualified to manage such situations. All adverse events are documented and handled according to the institutional policy of FVL. If necessary, participants may be referred to the institution’s emergency department, accompanied by the psycho-oncologist or a study representative, to initiate the required standard clinical care.

Ethical safeguards include respect for autonomy, confidentiality, and the right to withdraw at any time without affecting clinical care. Procedures are in place to minimize risk when addressing sensitive topics, including trauma-informed facilitation, private spaces for optional one-on-one counseling, and rapid referral pathways to psycho-oncology when indicated. All data will be deidentified and stored in secure, password-protected systems accessible only to authorized team members. Audio files and transcripts will be stored on secure institutional servers at the Clinical Research Center of FVL; identifiers will be removed during transcription, and a linkage file will be kept separately under restricted access. Paper materials (consent forms and checklists) will be stored in locked cabinets within restricted-access offices. Data retention will comply with institutional and national regulations. No photographs or video recordings of participants will be taken.

### Dissemination and Implementation Plan

In line with open science and transparency principles, we plan to disseminate study materials and outputs through (1) open access educational resources (eg, facilitator guides and modules) where appropriate, (2) interdisciplinary training workshops for health care providers to support culturally competent sexual health counseling in survivorship care, (3) presentations at relevant national and international scientific meetings and patient support networks, and (4) partnerships with academic and community stakeholders to support integration into clinical education and survivorship pathways. These activities aim to facilitate future replication and support sustainable incorporation of sexual health education into oncology survivorship care.

This protocol describes the rationale, intervention components, and mixed methods feasibility and acceptability evaluation of EDUSEXONCO, a co-designed, context-adapted educational psychosexual program for survivors of breast and gynecological cancer in Colombia. This study will assess implementation outcomes—including recruitment, retention, session attendance, fidelity to the manualized content, and completeness of quantitative and qualitative data collection—alongside participants’ acceptability and perceived usefulness of the intervention.

The findings will inform refinement of the EDUSEXONCO curriculum and delivery format (including prespecified contingency options) and will provide context-specific implementation knowledge to support integration of sexual health education into survivorship care pathways in low- and middle-income settings. Results from this feasibility study will also guide the design of a subsequent comparative, multisite study with longer follow-up to evaluate effectiveness and scalability.

## Results

This study is funded by the Women’s World Banking Colombia Foundation, awarded in December 2024, and received ethics approval from FVL. Recruitment began in March 2025 and is planned until September 2025. As of July 2025, a total of 13 participants have been enrolled (n=2, 15.4% with breast cancer and n=11, 84.6% with gynecological cancer). During feasibility activities, full-day sessions were identified as a potential barrier to attendance; accordingly, contingency adaptations (shorter session blocks and optional hybrid delivery) were suggested and will be considered as needed without altering protocol objectives or core content. Quantitative and qualitative data analysis is scheduled for October 2025; final results are expected by December 2025.

## Discussion

### Anticipated Findings and Contribution

This feasibility and acceptability study is designed to determine whether a co-designed, multidisciplinary educational psychosexual intervention (EDUSEXONCO) can be delivered as planned and is acceptable to survivors of gynecological and breast cancer in a Colombian university hospital setting. We anticipate generating actionable implementation evidence on recruitment and retention, session attendance, fidelity to the manualized content, and completeness of quantitative and qualitative data collection. In addition, we expect to identify participants’ perceived usefulness of the sessions, barriers to participation, and opportunities to refine content and delivery to better address sexual health needs during survivorship care.

### Comparison With Prior Work

Prior research has consistently documented that sexual health concerns are common among survivors of cancer and that health care professionals frequently report limited training, time constraints, and discomfort in addressing sexuality in routine oncology care [12,26]. Digital and blended interventions such as Fex-Can and Fex-Can 2.0 have shown that structured psychoeducational content, coupled with opportunities for reflection and support, can be acceptable and useful for survivors [13,14]. EDUSEXONCO is conceptually aligned with this body of work by combining evidence-informed education with multidisciplinary counseling and a supportive group environment to facilitate communication, normalize sexual concerns, and address survivorship-related changes in body image and intimacy. This approach also aligns with frameworks from the WHO and the WAS, which position sexual health as an integral component of health and a human right within survivorship care [17,19]. In Latin American contexts where stigma and sociocultural norms may discourage disclosure, group-based formats may offer a particularly valuable space for peer learning and validation; this feasibility study will help clarify how such delivery functions in the Colombian setting.

